### Main objective analysis

2.10

In order to study the dependency relationship between NLR and TILs, we will perform a correlation analysis between these 2 continuous variables (graphical analysis, Spearman correlation coefficient, significance test, confidence interval).

### Secondary objective analysis

2.11

The relationship between the other blood counts and the TILs at different times will be assessed through a correlation analysis as for the main objective.The relationship between the absolute blood counts and the derived ratios (NLR, PLR), and the response to NACT will be evaluated by analyses of variance (or Kruskal–Wallis tests) and logistic regressions. A subgroup analysis will be performed based on the length of the period between the last cycle of NACT and surgery. A mixed model will also be considered to account for repeated measures and the time lag between the end of NACT and surgery.The relationship between the presence of ctDNA after the end of treatment and the relapse of TNBC will be analyzed by Fisher's exact test. Patients treated with NACT and first-line surgery will be analyzed separately.The elements of blood will be assessed as early markers of TNBC relapse using logistic regressions, possibly penalized (the LASSO method). Patients treated with NACT and first-line surgery will be analyzed separately.

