### Secondary objectives and endpoints

2.3

Secondary objectives of the present study include:

Assessment of the correlation between the amount of TILs in the biopsy and the total white blood cell count (WBC), ANC, ALC, absolute platelet count (APC), and PLR routinely assessed in women with TNBC, at diagnosis.Assessment of the correlation between the mentioned blood counts and their ratios (NLR and PLR), at the time of diagnosis, and the response to NACT according to Sataloff.^[15]^Assessment of the correlation between the mentioned blood counts and their ratios (NLR and PLR) at the time of diagnosis, and the TIL amount in the post-NACT surgical specimen.Assessment of the correlation between the mentioned blood counts and their ratios (NLR and PLR) and the recurrence-free survival (RFS).Assessment of the correlation between the mentioned blood counts and their ratios (NLR and PLR) before post-NACT surgery and TIL quantity in the surgical specimen post-NACT, depending on the time between surgery and the last administration of chemotherapy.Assessment of the correlation between the mentioned blood counts and their ratios (NLR and PLR) and the presence of ctDNA.Assessment of the correlation between ctDNA and RFS.Assessment of the correlation between the mentioned blood counts and their ratios (NLR and PLR) after cancer treatment and the RFS.

The secondary endpoints include the following:

The absolute values of total white blood cells, neutrophils, lymphocytes, platelets measured in number of cells × 10^12^/L and the PLR at diagnosis. PLR is defined as the ratio of the APC over the ALC (PLR = APC/ALC).The values of total white blood cells, neutrophils, lymphocytes, platelets, NLR, and PLR before post-NACT surgery.TIL amount in the biopsy before cancer treatment.TIL amount in the surgical specimen post-NACT.Response to NACT according to the Sataloff classification.The period of time between surgery and the last administration of chemotherapy.The amount of ctDNA.Metastatic recurrence.

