### Study design

2.5

Eligible patients will be selected out of a local database of TNBC patients and will be recruited during the first year following the end of RT. The data collected before inclusion, such as TILs evaluation at baseline and in the surgical specimen, as well as blood test results at different times (baseline, before surgery, before the start of RT, and 6 months after the end of RT) will also be analyzed. After inclusion in the PERCEPTION trial, patients will undergo 2 interventions. A blood test will be performed 12 months after the end of RT and another blood test will be performed at the time of the first metastatic recurrence, if applicable. WBC, ANC, ALC, APC, NLR, PLR, and ctDNA will be measured from these blood tests. The overall follow-up is 5 years (see Fig. 1).

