### Data collection and management

2.7

Most of the data will be available and will have been collected at the time of enrolment:

Demographic data (age)Initial diagnosis of TNBC (date of diagnosis, histological characteristics of the tumor, hormone receptor and HER2 expression, TNM classification)Cancer treatment and response to the treatmentClinical characteristics of the tumor in the surgical specimenBlood test results at the time of diagnosis, before surgery, before the onset of RT, and 6 months post-RTTIL amount in the biopsy and in the surgical specimen

After patient enrolment, blood test results at 12 months post-RT and at the time of the first metastatic recurrence will be collected.

A comparison of the demographic and recurrence data of the recruited patients to those of eligible patients but not included in the study will be performed, to show that the studied population in this trial is no different from the general population of non-metastatic TNBC patients.

The assessment of TIL quantity will be independently performed by 2 breast pathologists. In case of the initial result discordance, the slides will be reviewed by both pathologists under a multi-headed microscope and the consensus will be reached after a concertation.

Tumor DNA mutations will be identified from tumor samples. Then, DNA will be extracted from the blood plasma and will be amplified by polymerase chain reaction (PCR), in order to select the DNA region carrying the mutation identified in the tumor sample and to measure the quantity of circulating tumor DNA.

Data will be collected and entered in the electronic Case Report Form (eCRF) by a Clinical Research Associate (CRA) in charge of the study, under the responsibility of the principal investigator.

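### The amount of ctDNA is a named secondary endpoint, but the only analysis naming ctDNA tests its presence against relapse; an analysis of the amount should be added

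*Protocol article*

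**What the plan says.** All references are to the protocol article.

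- **Endpoint (2.3, Secondary objectives and endpoints).** The list of secondary endpoints includes "The amount of ctDNA", a quantitative variable.
- **Objectives (2.3).** Two secondary objectives involve ctDNA. One relates the blood counts and their "ratios (NLR and PLR) and the presence of ctDNA", so it is worded as binary. The other reads "Assessment of the correlation between ctDNA and RFS" and leaves the form of ctDNA open.
- **Measurement (2.7, Data collection and management).** A mutation is identified in the tumour, then plasma DNA is amplified "to measure the quantity of circulating tumor DNA".
- **Sampling (2.5, Study design).** For the two samples taken after inclusion, at 12 months after radiotherapy and at first metastatic recurrence, "WBC, ANC, ALC, APC, NLR, PLR, and ctDNA will be measured from these blood tests".
- **Analysis (2.11, Secondary objective analysis).** The only item naming ctDNA is "The relationship between the presence of ctDNA after the end of treatment and the relapse of TNBC will be analyzed by Fisher's exact test". It adds: "Patients treated with NACT and first-line surgery will be analyzed separately". A further item reads "The elements of blood will be assessed as early markers of TNBC relapse using logistic regressions, possibly penalized (the LASSO method", without saying whether ctDNA is one of those elements.

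**The concern.** The endpoint list and the laboratory method treat ctDNA as a quantity, while the analysis section treats it as a yes/no finding. This is more than detail left to a fuller document: the article does fix an analysis for ctDNA, and fixes it on a different variable from the endpoint.

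The stake is moderate. Assessing ctDNA as a biomarker of metastatic recurrence is a stated aim (2.1). If relapse risk rises with the level among patients with detectable ctDNA, a 2×2 table cannot show it. The measurements will have been made and paid for, and the groups tested will be small.

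**Working it through.** **1. The plan's own figure.** Section 2.9 gives 90 patients for an effect size of 0.3, power 0.8 and alpha 0.05. Reading this as a two-sided test of a Spearman correlation (sidedness is not stated):

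n = 1.06 × [(1.960 + 0.842) / atanh(0.3)]² + 3 = 1.06 × (2.802 / 0.3095)² + 3 = 89.84, rounded up to 90.

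The figure reproduces. It belongs to the primary NLR–TIL correlation and says nothing about ctDNA. The article gives no ctDNA detection rate, relapse rate or level–risk relation, so everything below rests on assumed rates.

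**2. Main simulation.** Fix the numbers with and without relapse. Each patient is detected with probability p₁ (relapse) or p₀ (no relapse). The amount is 0 if undetected; otherwise it is lognormal with log-SD 1, the log-mean being higher by a shift d in relapsers. Compare Fisher's exact test on presence with the Mann–Whitney test on the amount, two-sided at 0.05. Power is the share of runs rejected.

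| Relapse / no relapse | p₁ / p₀ | d | Fisher, presence | Rank test, amount | Difference |
|---|---|---|---|---|---|
| 24 / 66 | 0.40 / 0.15 | 1 | 0.66 | 0.79 | 0.13 |
| 24 / 66 | 0.50 / 0.25 | 1 | 0.59 | 0.79 | 0.20 |
| 24 / 66 | 0.40 / 0.15 | 0 | 0.65 | 0.69 | 0.04 |
| 24 / 66 | 0.50 / 0.25 | 0 | 0.57 | 0.59 | 0.02 |
| 24 / 66 | 0.40 / 0.05 | 1 | 0.96 | 0.98 | 0.02 |
| 12 / 33 | 0.40 / 0.15 | 1 | 0.37 | 0.51 | 0.14 |
| 12 / 33 | 0.40 / 0.15 | 0 | 0.36 | 0.41 | 0.05 |

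The last two rows matter most, because 2.11 analyses the two treatment groups separately and no ctDNA test will have all 90 patients. The even split into 45 is an assumption. Repeat runs moved single values by up to about 0.03.

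**3. How much is Fisher's conservatism?** A large-sample test on the same presence data has power of about 0.70 (0.40/0.15) and 0.62 (0.50/0.25) in 24 v 66 patients. Of the 13 points in the first row, about 0.70 − 0.66 = 0.04 comes from the choice of test and 0.79 − 0.70 = 0.09 from using the level. In the second row the parts are 0.62 − 0.59 = 0.03 and 0.79 − 0.62 = 0.17. When the level is uninformative, the rank test roughly equals the large-sample presence test (0.69 v 0.70) or falls about 3 points short of it (0.59 v 0.62).

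**4. A second model.** Let logit P(relapse) = logit(0.20) + log(5) × detected + β × detected × log amount, with log amount standard normal.

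| N | Detectable | β = 0: Fisher v rank | β = 1 to 2: Fisher v rank |
|---|---|---|---|
| 90 | 15% | 0.71 v 0.76 | 0.66–0.67 v 0.76–0.77 |
| 90 | 30% | 0.91 v 0.91 | 0.83–0.87 v 0.95–0.96 |
| 45 | 15% | 0.39 v 0.45 | 0.40 v 0.52–0.54 |
| 45 | 30% | 0.57 v 0.60 | 0.53–0.55 v 0.72–0.75 |

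With no association at N = 90, rejection rates were 0.036–0.045 (Fisher) and 0.051–0.059 (rank), so conservatism contributes here too. The pattern is the same: a useful gain if the level carries information, little if it does not.

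**The case against.** **Presence is a declared form of the variable.** One objective in 2.3 is worded that way, and detected versus not detected is a sound question for an assay that looks for a mutation already found in the tumour. This stands. It is a reason to keep the Fisher test and not demote it, but it does not supply an analysis for the endpoint listed as an amount.

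**The amount may be analysed elsewhere.** A reader might infer that the amount is never analysed. The article does not support that: the regression item on blood elements could include ctDNA, which comes from the same samples as the counts, and 2.9 promises descriptive summaries of each variable of interest. What can be said is that no stated analysis relates the amount to relapse.

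**The cut-off.** A reader might also infer that, with no positivity threshold printed, the cut could be chosen once relapses are known. Nothing in the article suggests this. The natural reading of presence is detection by the assay, and a detection limit is detail that an article commonly leaves to the full protocol. Its absence is not a finding.

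**The power loss is assumed.** This stands in part. The large gaps need a level that differs between positive patients with and without relapse, and an appreciable positive rate among those without. With 5% positive there, the gap is 0.96 v 0.98.

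**The addition does not rescue the question.** Also fair: about 0.51 at 45 patients is still weak. A rank test by relapse status also ignores time and censoring, as Fisher's test does, although the objective is framed on recurrence-free survival.

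**Conclusion.** The point holds as a mismatch between endpoint and analysis: sections 2.3 and 2.7 make ctDNA quantitative, and the only analysis naming it in 2.11 is binary. Any information in the level is lost unless the regression item is meant to include it.

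The size is conditional. With 24 relapses among 90 patients, adding the amount is worth about 13 to 20 power points if the level is informative among positives, and about 0 to 5 points if it is not or if few patients without relapse are positive. At an assumed 45 per group the corresponding powers are about 0.37 v 0.51 and 0.36 v 0.41. The second model gives smaller informative gains at 90 (about 7 to 12 points) and gains of about 12 to 22 points at 45. Part of each range is Fisher's conservatism. A flat statement that the plan loses power would go beyond the documents. This is a modest, inexpensive improvement to a secondary analysis and does not affect the primary objective.

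**What to change.** In 2.11, add an analysis of the ctDNA amount at the 12-month post-radiotherapy sample against relapse, with undetected set to 0, alongside the presence/absence Fisher test and within the NACT and first-line-surgery groups as planned. A rank test would serve, or log(amount + 1) as a term in the relapse model; the latter depends on the unit of measurement, so state the unit. Naming the 12-month sample matters because the other post-inclusion sample is taken only at recurrence and has no comparison group. State also whether ctDNA is among the blood elements in the regression item.

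Cost: wording only, with no new samples or assays. The downsides are one more secondary test under the multiplicity correction promised in 2.9, little added information where few samples are positive, and an effect per unit of amount that is harder to report than a 2×2 table.

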**Methods::**

The main objective of this study is to evaluate the correlation between the peripheral neutrophil-to-lymphocyte ratio and the amount of tumor-infiltrating lymphocytes, assessed in triple negative breast cancer patients at diagnosis. Secondary objectives include evaluation of the correlation between tumor-infiltrating lymphocytes at diagnosis and the baseline absolute neutrophil, lymphocyte, and platelet counts, as well as the platelet-to-lymphocyte ratio. The triple negative breast cancer patients will be enrolled in the PERCEPTION trial during the first year after the treatment completion. Two supplementary blood tests, at 12 months after the end of treatment and at the time of the first metastatic recurrence, will be performed.

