Besides the full blood count, several studies have shown a correlation between the presence of circulating tumor DNA (ctDNA) in the blood and treatment response or even metastatic recurrence.^[10,11]^ Despite the insufficient data in TNBC, studies have shown that ctDNA is a reliable marker in predicting cancer recurrence, due to its high sensitivity and specificity.^[12,13]^ Moreover, this circulating biomarker can be obtained and quantified from a simple blood test. Therefore, evaluation of ctDNA as a predictor of metastatic relapse in TNBC is of great interest and it could provide additional information to that of TILs and/or the circulating blood cell counts.

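### The ctDNA–relapse test does not exclude the draw taken at relapse, nor require relapse to follow the draw used as exposure

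*Protocol article*

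**What the plan says.** The Introduction of the protocol article gives the purpose of the marker: "evaluation of ctDNA as a predictor of metastatic relapse in TNBC is of great interest". Section 2.1 makes ctDNA as a biomarker of metastatic recurrence a study aim of its own, and section 2.3 lists ctDNA against recurrence-free survival (RFS) as a secondary objective. The ctDNA endpoint in section 2.3 is an amount with no time point.

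Section 2.5 sets the draws made after inclusion. The first is at 12 months after radiotherapy; then "another blood test will be performed at the time of the first metastatic recurrence, if applicable". On what is assayed: "WBC, ANC, ALC, APC, NLR, PLR, and ctDNA will be measured from these blood tests". ctDNA is therefore measured at both.

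Section 2.11 sets the analysis: "The relationship between the presence of ctDNA after the end of treatment and the relapse of TNBC will be analyzed by" Fisher's exact test. It adds that neoadjuvant and first-line-surgery patients are analysed separately. It does not say which draw defines presence of ctDNA, or that relapse must come after that draw.

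Two other places bear on the reading. The abstract describes the draws as follows: "Two supplementary blood tests, at 12 months after the end of treatment and at the time of the first metastatic recurrence, will be performed". On the timing of inclusion, section 2.5 has patients recruited at any time in the first year after radiotherapy, whereas the Figure 1 caption places inclusion one year after it.

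**The concern.** Both scheduled draws fall after treatment, so the exposure as worded covers both. The second exists only because the outcome occurred, and it is taken when metastatic disease is already present. If it counts towards presence of ctDNA, relapsing patients have two chances to be positive and the others have one. The second chance also comes when a positive result is most likely. A sample taken at the event cannot predict the event.

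Fisher's test on a two-by-two table carries no time order, so it cannot correct this. The risk is that ctDNA is reported as a strong predictor of relapse when the 12-month sample carries no information.

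**Working it through.** **No figure to reproduce for this test.** The article gives no relapse share, ctDNA positivity rate or power for it. The sample size of 90 belongs to the primary correlation and plays no part in the argument beyond setting N.

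**Which draws fit the wording**

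| Draw | Who has it | After treatment? | Before relapse? |
|---|---|---|---|
| 12 months after radiotherapy | all included patients still followed | yes | yes, unless relapse came before month 12 |
| First metastatic recurrence | relapsing patients only | yes | no, taken at relapse |

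**Inputs**
- From the article: N = 90, nominal alpha 5% (taken as two-sided), Fisher's exact test.
- Assumed: n_R = 22 relapses (range 18–36). 12-month positivity q = 10% whatever the outcome (range 5–20%), so that ctDNA has no predictive value. Positivity at the relapse draw s = q, 50%, 60% or 80%. Draws are independent given these rates, and every relapsing patient has both.

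**Formulas**
- Positive at either draw, relapsing patients: p = 1 − (1 − q)(1 − s). Non-relapsing patients: q.
- Apparent odds ratio: OR = p(1 − q) / [(1 − p)q].
- Rejection rate: the sum over all tables (i, j) of Bin(i; n_R, p) × Bin(j; N − n_R, q), taken where the two-sided Fisher P is at most 0.05. This is exact enumeration.

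**Results, N = 90, 22 relapses, q = 10%**

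| Exposure | p in relapsing patients | OR | Rejection rate |
|---|---|---|---|
| 12-month draw only | 0.10 | 1 | 0.024 |
| Either draw, s = 10% | 1 − 0.9 × 0.9 = 0.19 | 2.1 | 0.17 |
| Either draw, s = 50% | 1 − 0.9 × 0.5 = 0.55 | 11 | 0.987 |
| Either draw, s = 60% | 1 − 0.9 × 0.4 = 0.64 | 16 | 0.999 |
| Either draw, s = 80% | 1 − 0.9 × 0.2 = 0.82 | 41 | 1.00 |

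**Sensitivity.** Over 18–36 relapses and q of 5–20%, the rates are 0.016–0.035 (12-month draw only), 0.10–0.34 (extra draw alone) and 0.89–1.00 (s = 50%).

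**Separate subgroups.** The article does not give the split, so 45 per subgroup is assumed. With 11 relapses and q = 10%, the rates are 0.021 (12-month draw only), 0.12 (extra draw alone), 0.86 (s = 50%) and 0.997 (s = 80%). Over 9–18 relapses and q of 5–20%, the extra draw alone gives 0.03–0.18 and s = 50% gives 0.62–0.96, against 0.003–0.032 with the 12-month draw only. At q = 5% the extra draw alone can stay below the nominal 5%, though it is still well above the 12-month-only rate.

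**Narrower reading.** Suppose the 12-month draw is meant, but a fraction f of relapsing patients relapse before month 12 and contribute a result taken at relapse. Then p = (1 − f)q + fs. With 22 relapses and q = 10%:
- f = 10%, s = 50%: p = 0.9 × 0.10 + 0.1 × 0.50 = 0.14, rejection rate 0.07.
- f = 25%, s = 50%: p = 0.20, rejection rate 0.20.
- f = 25%, s = 80%: p = 0.275, rejection rate 0.45.

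**The case against.** A reader might infer that the plan pools the two draws and counts any positive result. The documents do not support that. Section 2.11 does not say any, either or ever positive. The abstract ties the words about the end of treatment to the 12-month test and names the relapse test separately. The predictive purpose in the Introduction also fits only a draw before relapse. On that reading the second draw causes no circularity. One can add that a condensed article may leave the choice of sample to the full protocol or analysis plan, that the assumed rates are not in the documents, and that the Figure 1 caption would leave few or no patients relapsing between inclusion and month 12.

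Most of this stands, and it limits the finding to an exposure that is not fixed. It does not remove it. The article itself names the test, the exposure and the outcome, and as worded the exposure covers a draw that depends on the outcome. The narrower reading still does not require relapse to follow the draw, and section 2.5 allows recruitment early enough for relapse to precede month 12.

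A second tempting inference is that blood counts taken at relapse enter the early-marker regressions. Nothing says so. Section 2.11 does not list the time points, the word early argues against it, and counts from diagnosis to 6 months after radiotherapy are available whether or not a patient relapses.

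**Conclusion.** The concern holds as a gap in definition. The ctDNA–relapse analysis does not exclude a draw that only relapsing patients have, and it does not put exposure before outcome.

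The size depends on how the gap is filled. With the 12-month draw only and all relapses after it, the test keeps its level (about 2% under the assumed rates). If the relapse draw counts, a null marker is declared associated in about 17% of trials from the extra draw alone, and in about 99% or more if 50–80% are positive at relapse. If only early relapses contribute a relapse-time result, the rate runs from 7% to 45% in the scenarios shown. Subgroup rates are generally lower but remain above those from the 12-month draw alone. All these figures are conditional on assumed relapse and positivity rates and are not forecasts of the trial's result.

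This concerns a secondary objective, though one tied to a stated study aim. The primary correlation between the neutrophil-to-lymphocyte ratio and tumor-infiltrating lymphocytes, and the sample size of 90, are unaffected.

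**What to change.** Add a paragraph to section 2.11:

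- Exposure is the ctDNA result from the draw 12 months after radiotherapy.
- The analysis set is patients relapse-free at that draw, and only later relapses count.
- The preferred outcome is time from that draw to relapse, which matches the RFS objective in section 2.3. Fisher's test may stay as a supplement on the same set; it is free of this circularity once the landmark is in place.
- The relapse-time sample is used descriptively only, for example as change from month 12.
- Relapses before month 12 are counted and reported separately.
- For blood counts, state that values taken at relapse are not used as predictors and that 12-month counts follow the same landmark.

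Also reconcile the inclusion timing in section 2.5 with the Figure 1 caption, since it determines how many early relapses can occur in the study.

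The cost is one paragraph, with no new samples or patients. The downside is that patients relapsing before month 12 leave this secondary analysis, so its conclusions apply only to patients relapse-free at one year.

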### Eligibility criteria

2.4

The participants should meet the inclusion criteria in order to be enrolled in the study (see Table 1). Only adult (over 18 years of age) female patients diagnosed for the first time with non-metastatic TNBC will be recruited. The eligible patients must be treated with chemotherapy, surgery, and radiation therapy (RT). The lack of tumor sample from biopsy, necessary for the evaluation of TILs and the lack of blood test results at diagnosis will render the inclusion impossible.

**Table 1 T1:** Inclusion and exclusion criteria of the PERCEPTION trial.

Inclusion criteria	Exclusion criteria
Female	Unavailable biopsy tumor samples
Age ≥18 yr	Unavailable blood test results at the time of diagnosis
Primitive, non-metastatic triple negative breast cancer, diagnosed histologically	Pregnant or breastfeeding women, vulnerable persons, adults under legal protection, or unable to give their consent, according to the L.1121-6 article of the Public Health Code
Treated with chemotherapy, surgery, and radiation therapy	
French language fluency	
Affiliation to social security	
Able to provide a signed informed consent form	

Patient may exit study prematurely following:

-Patient decision-Investigator decision-Patient death-Patient lost to follow-up

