### Recruitment

2.6

Recruitment will be carried out in the Jean Perrin Centre by an oncologist. After checking the inclusion and exclusion criteria, the study will be thoroughly explained to the patient by the oncologist, and a consent form will be signed by both.

The recruitment period will last 3 years, from October 2019 to October 2022; 90 patients are expected to be included. After enrolment completion, the primary objective will be analyzed. The overall follow-up for each patient is 5 years, if no metastatic recurrences occur.

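### Three secondary objectives are stated on recurrence-free survival, but the analysis section treats relapse as yes/no and names no time-to-event method

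*Protocol article*

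**What the plan says.** Section 2.3 (Secondary objectives and endpoints) names RFS in three objectives:

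- blood counts and ratios: "Assessment of the correlation between the mentioned blood counts and their ratios (NLR and PLR) and the recurrence-free survival (RFS"
- ctDNA: "Assessment of the correlation between ctDNA and RFS"
- post-treatment blood counts and ratios, where the same correlation is sought between values "after cancer treatment and the RFS"

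The endpoint list in the same section ends with "The amount of ctDNA.Metastatic recurrence". It contains neither RFS nor time to an event nor death.

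Section 2.11 (Secondary objective analysis) gives the methods. For ctDNA: "The relationship between the presence of ctDNA after the end of treatment and the relapse of TNBC will be analyzed by" Fisher's exact test. For blood counts: "The elements of blood will be assessed as early markers of TNBC relapse using logistic regressions, possibly penalized (the LASSO method".

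On observation time, section 2.6 (Recruitment) states: "The overall follow-up for each patient is 5 years, if no metastatic recurrences occur". Section 2.4 lists reasons for leaving early, among them "Investigator decision-Patient death-Patient lost to follow-up". Section 2.5 has patients enter during the first year after radiotherapy (RT). It places the study blood samples, including ctDNA, at 12 months after RT and at the first metastatic recurrence.

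**The concern.** RFS is a time-to-event outcome. It needs a list of events, a time origin and a censoring rule. Fisher's test and logistic regression need only a yes or no for each patient, and they answer a different question: the odds of an observed relapse.

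The article does more than leave detail to another document. It names specific methods, and they do not fit three of its own objectives. An analysis plan that followed section 2.11 faithfully would inherit the mismatch.

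At stake is the prognostic part of the study. Section 2.1 makes ctDNA as a marker of metastatic recurrence a study aim, and section 2.11 splits the relapse analyses further by neoadjuvant chemotherapy versus first-line surgery. With few events, both the timing information and the handling of early exits matter.

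**Working it through.** **Step 1. Objective, endpoint and method side by side.**

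| Objective (2.3) | Outcome named | Endpoint listed (2.3) | Method (2.11) |
|---|---|---|---|
| Blood counts and ratios | RFS | Metastatic recurrence | Logistic regression, possibly LASSO |
| ctDNA | RFS | Metastatic recurrence | Fisher's exact test |
| Post-treatment counts and ratios | RFS | Metastatic recurrence | Logistic regression, possibly LASSO |

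No Kaplan-Meier, log-rank, Cox or competing-risk method and no censoring rule appears. The mixed model in section 2.11 concerns repeated measures and the interval from chemotherapy to surgery, not RFS.

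**Step 2. Who cannot be classified.** A patient who dies or is lost at time c < 5 years without relapse has no defined yes/no value. Coded as relapse-free, a patient lost after one year counts the same as one followed for five. Dropped, patients are selected on having stayed or having relapsed early. Neither handles RFS, in which a death is conventionally an event and a lost patient contributes time up to censoring.

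**Step 3. The plan's own figure.** Section 2.9 gives 90 patients for effect size 0.3, power 0.8 and alpha 0.05. For a two-sided Spearman test:

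N = 3 + 1.06 × ((1.960 + 0.842) / atanh 0.3)² = 3 + 1.06 × (2.802 / 0.3095)² = 89.8, rounded up to 90.

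This reproduces, but it belongs to the primary correlation. No event count or power is stated for RFS.

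**Step 4. Illustrative size.** The documents supply only N = 90 and the 5-year follow-up. Everything else is assumed:

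- standard normal marker, hazard ratio (HR) 1.5 per SD for relapse and for death without relapse
- constant hazards, λ = −ln(1 − p)/5, where p is the 5-year risk at the average marker value: 0.0446, 0.0713 and 0.1022 per year for 20%, 30% and 40% recurrence; 0.0103 for 5% deaths; 0.0211 for 10% loss
- loss unrelated to the marker; exits coded as no relapse in the logistic model
- 800 simulated trials per row, so a Monte Carlo standard error of at most √(0.25/800) = 0.018 per figure

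| 5-year recurrence | Deaths / loss | Logistic power | Cox power | Difference (points) |
|---|---|---|---|---|
| 20% | 0 / 0 | 0.390 | 0.412 | 2.2 |
| 30% | 0 / 0 | 0.530 | 0.546 | 1.6 |
| 40% | 0 / 0 | 0.655 | 0.685 | 3.0 |
| 20% | 5% / 10% | 0.352 | 0.464 | 11.2 |
| 30% | 5% / 10% | 0.459 | 0.565 | 10.6 |
| 40% | 5% / 10% | 0.564 | 0.704 | 14.0 |

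In the last three rows, on average 3.4–4.0 deaths and 6.7–7.9 lost patients per trial were counted as relapse-free. Part of the gap is Cox gaining, because the deaths were assumed to follow the marker. From the first three rows to the last three, logistic power falls by 3.8, 7.1 and 9.1 points, while Cox power rises by 5.2, 1.9 and 1.9.

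**Step 5. Direction of bias.** A second simulation assumed 90 patients, 65% 5-year RFS with a front-loaded hazard, 25% exits rising with the marker at HR 2.2 per SD, and no true marker effect. The mean logistic odds ratio was about 0.9 with exits coded as relapse-free and 1.23 with exits dropped; the Cox hazard ratio averaged 1.01. The sign of the bias therefore depends on a coding rule the article does not state.

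**The case against.** The case for a milder reading is substantial, and much of it stands.

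- **The objectives are secondary.** The primary Spearman correlation of the neutrophil-to-lymphocyte ratio with tumour-infiltrating lymphocytes, and its sample size, are unaffected. Nor would Cox make the relapse analyses confirmatory: its power is only 0.41–0.70 in the table.
- **A common 5-year horizon is planned.** If fully observed, relapse within 5 years is a legitimate outcome and little power is lost. Rewording the objectives that way would remove the contradiction, but patients who die or are lost early would still need a rule.
- **Only the article is shown.** It cites version 14 of the full protocol. That RFS is not analysed can be said only of the article.

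Three stronger readings are tempting but unsupported:

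- **That the plan biases results towards the null or creates a false protective effect.** This needs exits strongly related to the marker and coded as relapse-free. The documents state neither, and dropping exits reverses the sign. With no marker effect, the logistic false-positive rate was 0.040 when 10% loss was unrelated to the marker. It was 0.045 with 20% loss at HR 1.5 per SD, and reached 0.086 (Cox 0.053) only with 30% loss at HR 2 per SD.
- **That much larger power losses should be expected.** Losses of 13–18 points arise with 10% deaths, 20% loss and analysis at unequal follow-up of 2–5 years. Section 2.6 schedules only the primary analysis at the end of enrolment, so early relapse analysis is not the stated plan.
- **That section 2.4 codes death as a non-event.** It lists reasons for leaving the study and says nothing about coding. Taking death off the list would correct nothing.

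**Conclusion.** The mismatch is a wrong stated method on secondary objectives and should be fixed. Three objectives name RFS, the endpoint list does not carry it, and the stated methods ignore time and have no place for censoring or for deaths without relapse. This rests on the text alone.

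The size does not. It is small, about 2–3 power points, if every patient is followed for 5 years and none dies without relapse. It is about 10–14 points under the assumed 5% deaths and 10% loss, with deaths following the marker as relapse does. Bias is possible under either treatment of early exits, but its direction and extent cannot be read from the documents.

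**What to change.** **Section 2.3.** List RFS as an endpoint, with its events (recurrence or death from any cause), its time origin, and censoring at last contact. Metastatic recurrence may stay as a further endpoint, with death as a competing event.

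**Section 2.11.** For the RFS objectives, replace Fisher's test and logistic regression by Kaplan-Meier curves with log-rank tests and Cox models, using penalised Cox where variable selection is wanted. Then:

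- for markers measured at diagnosis or otherwise before enrolment, use delayed entry at the enrolment date, since patients join at different points in the year after RT
- for ctDNA and counts taken 12 months after RT, start the clock at the sampling date (a landmark). Delayed entry at enrolment is not enough here, because a patient must remain under observation to be sampled and the time before sampling would be counted as event-free by construction
- do not use samples taken at recurrence as predictors of recurrence

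**Cost.** Wording in two sections, with no extra patients or blood tests. The electronic case report form must hold dates of recurrence, death and last contact; section 2.7 does not list the dates of death or last contact. The landmark analysis excludes patients who relapse before their 12-month sample, and this should be reported.
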